## Abstract

**Background:**

Obesity in women with polycystic ovary syndrome (PCOS) negatively affects all clinical features, and a 5 to 10% weight loss has shown promising results on reproductive, metabolic and psychological level. Incorporating a healthy diet, increasing physical activity and changing dysfunctional thought patterns in women with PCOS are key points in losing weight. The biggest challenge in weight management programs is to achieve a reasonable and sustainable weight loss. The aim of this study is to explore whether Cognitive Behavioural Therapy (CBT) by a mental health professional, working in a multidisciplinary team with a dietician and a physical therapist (a three-component intervention), is more effective for weight loss in the long term, within 12 months. We will also explore whether mobile phone applications are effective in supporting behavioural change and sustainable weight loss.

**Methods:**

The present study is a longitudinal randomized controlled trial (RCT) to study the effectiveness of a three-component 1-year cognitive-behavioural lifestyle intervention in overweight/obese women with PCOS. A total of 210 participants are randomly assigned to three groups: 1) CBT provided by the multidisciplinary team or; 2) CBT provided by the multidisciplinary team and Short Message Service (SMS) or; 3) usual care: encourage weight loss through publicly available services (control group). The primary aim of the 12-month intervention is to explore whether a three-component 1-year cognitive-behavioural lifestyle intervention is effective to decrease weight, when compared to usual care. Secondary outcomes include: the effect of the intervention on the PCOS phenotype, waist circumference, waist to hip ratio, ovulation rates, total testosterone, SHBG, free androgen index (FAI), AMH, hirsutism, acne, fasting glucose, blood pressure and all psychological parameters. Additionally, we assessed time to pregnancy, ongoing pregnancies, clinical pregnancies, miscarriages and birth weight.

All outcome variables are measured at the start of the study, and again at 3 months, 6 months, nine months and 12 months.

**Discussion:**

We expect that CBT provided by a multidisciplinary team, especially combined with SMS, is effective in developing a healthy lifestyle and achieving a long-term weight loss in women with PCOS. Losing 5– 10% body weight improves various PCOS characteristics. Consequently, we expect to show that CBT provided by a multidisciplinary team improves reproductive and metabolic outcomes, as well as quality of life, while at the same time being cost-effective.

**Trial registration:**

Registered at the Netherlands National Trial Register with number NTR2450 on August 2nd, 2010.

## Plain English summary

Obesity in women with polycystic ovary syndrome (PCOS) negatively affects all clinical features, and a 5 to 10% weight loss has shown promising results on reproductive, metabolic and psychological level. Incorporating a healthy diet, increasing physical activity and changing dysfunctional thought patterns in women with PCOS are key points in losing weight. The present study is a longitudinal randomized controlled trial (RCT) to study the effectiveness of a three-component 1-year cognitive-behavioural lifestyle intervention in overweight/obese women with PCOS. We will also explore whether mobile phone applications are effective in supporting behavioural change and sustainable weight loss. The primary aim of the 12-month intervention is to explore whether a three-component 1-year cognitive-behavioural lifestyle intervention is effective to decrease weight, when compared to usual care. We expect that CBT provided by a multidisciplinary team, especially combined with SMS, is effective in developing a healthy lifestyle and achieving a long-term weight loss in women with PCOS. Losing 5– 10% body weight will improve various PCOS characteristics. Consequently, we expect to show that CBT provided by a multidisciplinary team improves reproductive and metabolic outcomes, as well as quality of life, while at the same time being cost-effective in women with PCOS.

## Background

Polycystic ovary syndrome (PCOS) is a common endocrine disorder that affects 5–10% of women in their reproductive years [1]. According to the ESHRE/ASRM Rotterdam consensus [2], the diagnosis of PCOS requires at least 2 of the following 3 criteria: oligoovulation or anovulation (irregular or no menstrual cycle at all), clinical (hirsutism) and/or biochemical signs of hyperandrogenism (elevated free androgen index or elevated testosterone levels), polycystic ovarian morphology (on ultrasound), and the exclusion of other aetiologies that might cause hyperandrogenism. PCOS women will generally experience one or more of the following symptoms in varying degrees: hirsutism (excessive body hair growth), acne, anovulatory infertility, obesity, insulin resistance and dyslipidaemia [2, 3].

The incidence of overweight and obesity in PCOS women is between 50 and 60% [3]. The prevalence of obesity in the general population is increasing, and this might result in an even higher incidence of PCOS in the future [4, 5]. The current prevalence of overweight and obesity is significantly higher in PCOS women, especially in Caucasian women [6]. Overweight in women with PCOS negatively affects all clinical features [3, 7–9] and gaining weight aggravates also psychological aspects. Women with PCOS report a major impact on their quality of life (QoL) due to PCOS symptoms [10, 11] and experience more distress compared to women without PCOS [12]. Weight concerns in particular appear to have the largest impact on QoL, compared to other PCOS symptoms such as amenorrhea, oligomenorrhea, hirsutism and acne [13]. Obesity is also a risk factor for lower self-esteem and greater sexual dissatisfaction in women with PCOS, compared to age matched controls [14, 15]. PCOS women with amenorrhoea seem to have lower levels of self-esteem and greater fear of negative appearance compared to PCOS women with oligo-amenorrhea [16].

Whether PCOS women have a unique predisposition to obesity is not yet clear [17]. A recent study by Louwers et al, looking into the genetic predisposition for overweight or obesity, did not discover any differences in the number of risk alleles for obesity between women with PCOS and the controls [18]. Although women with PCOS generally do have a healthy diet, they seem to have a higher caloric intake and are physically less active, compared to controls without PCOS [19]. Also, women diagnosed with PCOS more often use a self-initiated inadequate diet than controls [20]. Insulin resistance might play a mediating role in the effect of obesity on metabolic and reproductive symptoms in PCOS [21]. Other authors do suggest that the high prevalence of obesity might be a result of selection and referral bias of obese PCOS women [22]. In summary, much about the link between PCOS and obesity remains unknown [1]. It is still unclear whether obesity is the cause, or an effect of the disease itself [6, 23].

There is a large number of small (one or two-component) studies demonstrating that losing 5 to 10% of initial body weight improves reproductive, metabolic and psychological features in PCOS women [24]. Moreover, it often leads to ovulation and subsequent pregnancy, [7, 25–27] as well as a reduction in miscarriage rates in PCOS women [4, 7]. Weight loss also reduces the risk of Type II Diabetes Mellitus and the incidence of the metabolic syndrome in the long term [7, 27]. Additionally, studies have indicated that decreasing intra-abdominal fat tissue in particular results in the restoration of ovulation [28], even when women remain within their World Health Organisation (WHO) weight class after weight loss [29, 30]. Recent work from Mutsaerts et al [31] and Dokras et al [32] showed different results. A mean weight loss of 4.4 kg following a two-component lifestyle treatment of 26 weeks did not result in a significant difference in live birth rates compared to a weight loss of 1.1 kg in the control group. Also, there was no difference in pregnancy and neonatal complications between groups [31]. Weight loss by the Look AHEAD protocol (16 weeks) or the use of the oral contraceptive pill shows significant improvement in both groups at physicial and mental domains related to quality of life, depression and anxiety [32]. At the ESHRE/ASRM PCOS meeting in 2010, a consensus was reached that lifestyle should be optimized before conception [23] to improve the effectiveness of fertility treatment [33, 34] and to improve (mental)health across a woman’s lifespan as well as that of her child to be [27]. However, no international evidence based protocol exists for the long-term treatment of overweight and obesity in this particular group of obese women [35].

The biggest challenge in weight management programs is to achieve a reasonable and sustainable weight loss [36, 37]. Many obesity interventions compare one-component (physical activity or nutrition intervention) with two-component (physical activity and nutrition or nutrition and counselling) interventions. Three-component (physical activity, nutrition and counselling) lifestyle interventions seems to have the biggest effect, compared to one or two components [38]. Weight loss programs in general seem to be effective in the short term [39]; however, most of the initial weight loss is regained within 1 year [36]. Long term weight-loss seems the biggest challenge for the “global obesity epidemic” according to the WHO [40]. Incorporating a healthy diet, increasing physical activity and changing dysfunctional thinking patterns in women with PCOS are key points in losing weight [41]. However, treatment adherence is often low [36] and drop-out rates are high. The longer the treatment, the higher the chance for participants to drop-out, and indeed the highest dropout rates are reported in interventions that last 24 weeks or longer [42]. This relation between the drop-out rate and the duration of therapy is particular worrying, as long lasting lifestyle changes are preferred. Patients who are likely to drop out will benefit most from adherence to a long-term lifestyle program compared to patients not at risk to drop out. Fauser et al. commented that more research is needed to optimize lifestyle interventions, maximizing weight loss and minimizing drop-out rates for PCOS women with a wish to conceive [23].

A possible solution to increase therapy adherence and reduce the drop-out rate is support by mobile phone applications. Weight loss interventions making use of internet and mobile phone applications have emerged to induce behavioural changes [43]. There is a growing body of literature on Short Message Service (SMS) and smart phone interventions for obesity treatment, indicating that tailored text messages are more effective than generic ones [44, 45]. Smart phone and mobile phone applications seem effective when embedded in an intervention program [46]. Studies have indicated that sending SMS results in weight maintenance up to 12 months after completion of cognitive behavioural treatment (CBT), [47] and supports controlling the desire to eat and promoting an active lifestyle [48]. Moreover, the use of SMS has shown to improve adherence and decrease the drop-out rates in weight loss treatments [49], which is associated with improvement in weight-related behaviours and weight outcomes [50].

Fauser et al. commented that more research is needed to optimize lifestyle interventions, maximizing weight loss and minimizing dropout for PCOS women with a wish to conceive [23].

## Methods/design

### Aim

The aim of this study is to examine whether CBT, provided by a mental health professional working in a multidisciplinary team with a dietician and a physical therapist (a three-component intervention), is effective to decrease weight, compared to usual care at the end of treatment in obese women with PCOS. Furthermore, we explore whether mobile phone applications are effective in supporting behavioural change and sustainable weight loss.

### Research hypotheses

Primary:A multidisciplinary 1-year cognitive-behavioural lifestyle intervention (with or without SMS) is more effective to decrease weight in 12 months, compared to usual care.

Secondary:2)A multidisciplinary 1-year cognitive-behavioural lifestyle intervention (with or without SMS) is effective to decrease weight by 4.0 BMI points at 12 months, compared to usual care.3)SMS maintenance treatment in combination with a multidisciplinary 1-year cognitive-behavioural lifestyle intervention is more effective than the multidisciplinary 1-year cognitive-behavioural lifestyle intervention alone, in terms of weight loss maintenance and drop-out reduction.4)A multidisciplinary 1-year cognitive-behavioural lifestyle intervention (with or without SMS) is effective in improving the menstrual cyclicity as well as anthropomorphometric, ultra-sonographic, endocrine and psychological parameters in women with PCOS.

### Design

The present study is a longitudinal RCT measuring the effectiveness of a three-component multidisciplinary 1-year cognitive-behavioural lifestyle intervention in overweight/obese women with PCOS. It is a three-armed RCT comparing three groups: 1) CBT provided by a multidisciplinary team or; 2) CBT provided by a multidisciplinary team and Short Message Service (SMS) or; 3) usual care: encouraged to lose weight by publicly available services (control group), see Fig. 1.

**Fig. 1 Fig1:**
[figure not shown]
CONSORT 2010 standard RCT flow diagram

Patients will be included in the trial at the department of Obstetrics and Gynaecology of the Erasmus MC in Rotterdam, the Netherlands.

### Participants

Women with menstrual cycle disorders are systematically screened using the same standardised protocol i.e. the so called CyclusOLigoAmenorroe (COLA) protocol. The COLA protocol includes a family and reproductive history, antropomorphometric, ultrasonographic assessments and screening. Based on this screening, women are diagnosed according the World Health Organisation (WHO) classification. Women with WHO 2 normogonadotropic normo-estrogenic anovulation are further classified using the Rotterdam consensus criteria for PCOS and non-PCOS. Patients who meet the inclusion and exclusion criteria (shown in Table 1) are eligible. At enrolment, all patients receive detailed information about the role of weight loss in PCOS and the benefits of lifestyle modification.

**Table 1 Tab1:** Eligibility

Inclusion criteria:	Exclusion criteria:
✓PCOS according to Rotterdam consensus criteria [2]	✓Women with inadequate command of the Dutch language
✓Body mass index (BMI) > 25 kg/m^2^	✓Mental illness
✓Age between 18 and 38 years	✓Obesity with another somatic cause
✓Trying to conceive over 1 year	✓Ovarian tumours that lead to an androgen excess
	✓Adrenal diseases
	✓Other malformations of internal genitalia
	✓Pregnancy

The gynaecologist presents the patient information about the study using a patient information leaflet. After 2 weeks, patients are contacted by telephone in order to assess whether they are willing to participate in the study. In order to participate, patients need to sign the informed consent form and return it by regular mail. As soon as this form is received out our research office, appointments for baseline measurements are made.

### Randomisation

At the baseline, after the initial assessment, participants are randomized at a 2:1 ratio into the following groups: 1-year CBT lifestyle intervention with SMS (*n* = 78), 1-year CBT lifestyle intervention without SMS (*n* = 78), or the control group who receives usual care (*n* = 78) using a computer-generated random numbers table. A research nurse, who is not involved in the study, carries out the randomisation. Assignment is made by sequentially numbered, identical, sealed envelopes, each containing a letter designating the allocation (i.e. “A” for intervention with SMS, “B” for intervention without SMS and “C” for control,).

### Intervention

The 1-year multidisciplinary lifestyle intervention aims at: 1) changing cognitions; 2) changing dietary habits; 3) encouraging and promoting physical activity; and 4) activating social support; and consists of twenty 2.5 h group sessions. The first 1.5-h of every group session is supervised by a mental health professional and a dietician. The last hour of each session is supervised by a physical therapist. Each lifestyle intervention group consists of a maximum of 10 patients to ensure that there is sufficient individual attention for every participant. Additionally, participants receive five individual counselling sessions of 45 min with a mental health professional, five individual sessions with a physical therapist and five with a dietician.

We developed the “PCOS lifestyle textbook” for participants, which describes the activities of each group session and the homework assignments. To standardize the treatment and to facilitate the therapist’s treatment adherence, we developed a therapist manual, which includes protocols for each session. The manual also includes PowerPoint slides to present at each group session.

#### Phase 1: first 3 months (session 1 to 11)

We divided the 20 group sessions into four phases. The outline of each session is presented in Table 2. In the first phase of the program, the group sessions are held weekly. CBT techniques are used to create awareness and to restructure dysfunctional thoughts about lifestyle (food & exercise), weight (loss) and self-esteem. The Dutch food guide (DFG) is used as a guideline for healthy eating and is the main guideline during the nutritional sessions run by the dietician. Subjects receive the DFG guide for women aged 19 to 50 (Table 3) [51]. Based on the DFG, a healthy woman with a normal weight and regular exercise, may take in up to 2000 kilocalories in total, consisting of 1700 kilocalories for breakfast, lunch and dinner, and another 300 kilocalories for (healthy) snacking. The take-up of 2000 kilocalories in total is normally advised for weight maintenance. Hence, for most women in the lifestyle program this (reduced intake) will result in weight loss. During phase 1, we emphasize that participants should start making healthy, sustainable food choices and to avoid “restrained” behaviour like skipping meals and reducing food variance [52].

**Table 2 Tab2:** Overview of the content of the lifestyle intervention

Session	Topic	Objectives
1	Introduction	Introduction of the therapists and the group members. Agreement on attendance, commitment, homework assignments, privacy and buddy system. Providing information about the program and target weight. Providing information about the concept of energy balance. Explaining the link between thoughts, feelings and behaviors.
2-4	Diet: Explaining the Dutch food guide and daily amounts Psychology: introduction of cognitive behavior therapy	Providing information about the Dutch Food Guide (DFG). Increasing or decreasing daily amounts based on the Dutch Food Guide (DFG) Identifying unhealthy food choices. Understanding the rationale of cognitive behavior treatment. Completing a thought record. Setting realistic goals (proactive coping).
5	Partner and social support meeting	Welcome to spouses (or family/friends) General introduction of the lifestyle program for spouses (or family/friends). How to be supportive in a helpful way. Providing information about the concept of energy balance.
6,7	Diet: Reading food nutrition labels Psychology: Biased perception and interpretation	Participants are able to read food nutrition labels. Making healthier choices based on food nutrition labels. Identifying and correcting biased perception and interpretation.
8	Dealing with infertility	Sharing emotions concerning infertility. Reframing negative thoughts concerning infertility.
9,10	Binge eating	Learning different incentive values of food. Obtaining a regular eating pattern (breakfast, lunch and dinner). Knowing the difference about hunger, appetite sensations and binge eating.
11	Partner and social support meeting	Using different preparation techniques for cooking. Asking help from spouses.
12	Binge eating	Finding alternate ways to handle binge eating Eating healthy portion sizes.
13	Diet: dealing with the holidays or special occasions Psychology: Behavioral experiment	Making a meal plan for the holidays. Explaining the rationale for behavioral experiments. Setting up behavioral experiments.
14	Mindful eating	Knowing the difference between conscious and unconscious eating. Introduction of mindfulness techniques.
15	Diet: Snacks Psychology: Relapse prevention	Learning the difference between healthy and unhealthy snacking. Identifying difficult moments and finding alternative thoughts. Reframing dysfunctional cognitions concerning relapse.
16	Diet: Eating in a restaurant Psychology: assertiveness	Eating a healthy meal in a restaurant. Performing a roll-playing game in a restaurant. Saying no in a food related situation.
17	Partner and social support meeting	Doing the healthy eating quiz. Doing a cue exposure exercise involving sweets and cookies.
18,19	Diet: Healthy pregnancy Psychology: Relapse prevention	Identifying and preventing relapse moments. Developing self-efficacy beliefs for the future. Dealing with food and appetite sensations during pregnancy.
20	Evaluation of the program Relapse prevention	Evaluation of the lifestyle program and participants progress. Providing information about long-term weight maintenance. Coping with regaining weight.

**Table 3 Tab3:** Dutch Food Guide (women, age group 19–50 years)

Vegetables	200 g
Fruit	200 g (2 servings)
Bread	6 slices
Potatoes, rice, pasta or beans	200 g
Milk	450 ml
Cheese	1,5 slice
Meat	100 g
Butter and oil	30 g
Drinks	1,5 liter
(Healthy) Snacks	300 calories

The physical therapist encourages participants to use exercise as part of their daily routine, [53] according to the Global Recommendations for physical activity by the World Health Organisation, [54] and advises:To do 5 days of moderate physical activity for 30 min each day; andTo do vigorous exercise 1 to 3 days a week, for at least 20 min per session; andTo perform 8 to 10 muscle-strengthening activities involving major muscle groups twice a week.

#### Phase 2: month 3 to 6 (session 12 to 16)

In the second phase of the program, the group sessions are held once every two weeks. During this phase participants are motivated to develop a structured eating pattern to avoid over-restriction and under-restriction, like binge eating and restrained eating [55]. The frequency of face-to-face contact decreases over time, to stimulate participants to maintain healthy eating and physical activity. This is based on the principles of ‘proactive coping’ to promote self-regulation [56]. Also, behavioural skills developed during phase 1 of the intervention are reinforced [57].

#### Phase 3: month 6 to 9 (session 17 to 19)

In the third phase of the program, the group sessions are held once a month. Participants learn about relapse management and maintenance of their weight loss. By using proactive coping, participants set new goals for the next 3 months aimed at maintaining a healthy lifestyle. Individual counselling sessions are planned if needed at the request of the participant.

#### Phase 4: final 3 months (session 20)

During the final 3 months of the program, there are no scheduled group sessions. Participants can contact the multidisciplinary team if individual counselling sessions are needed.

There is an outreach policy to motivate participants to come to the measurement sessions, unless the participant indicates to withdraw from the study. Participation in the lifestyle intervention terminates if the participant misses more than 3 out of 20 group sessions. In such cases, the measurements will also stop. For obvious reasons, the intervention and the measurements will also stop when the participant is pregnant.

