### Outcome measures

The primary outcome of this study is to test whether CBT provided by a mental health professional, working in a multidisciplinary team with a dietician and a physical therapist (a three-component intervention), is effective to decrease weight compared to usual care (control) at the end of the treatment. Secondary outcomes include: reproductive, drop-out, quality of life, healthy diet, physical activity, metabolic and endocrine improvements, the health of the (unborn) child. All outcome variables are measured at the start of the study, and again at 3 months, 6 months, 9 months and 12 months. All outcome measures are displayed in Table 6. Below we give more details about the collection of the secondary outcomes.

**Table 6 Tab6:** Outcomes measures (T0, T1, T2, T3, T4)

Primary outcome	
Weight in kilograms	
Secondary outcomes	
(1) reproductive outcomes:	a) cycle duration and frequency
	b) spontaneous pregnancies
2) anthropomorphometric outcomes:	a) BMI
	b) waist circumference (WC)
	c) hip circumference (HC)
	d)WC/HC ratio
(3) clinical and biochemical PCOS features:	a) hair growth pattern
	- Ferriman Gallwey score
	b) blood pressure
	c) transvaginal ultrasound outcomes
	- ovarian volume
	- follicle count
	- total follicles per ovary
	d) endocrine outcomes
	- insulin resistance
	- hyperandrogenism
	- dyslipidemia
(4) psychological outcomes:	a) eating behaviour and disturbances
	- The Dutch Eating Behaviour Questionnaire (NVE)
	- Eating Disorder Examination Questionnaire (EDE-Q)
	b) quality of Life
	- Short Form 36 (SF-36)
	- Polycystic Ovary Syndrome Questionnaire (PCOSQ)
	c) depression
	- Beck Depression Inventory (BDI)
	d) self-esteem
	- Rosenberg Self Esteem Scale (RSE)
	e) fear of negative appearance
	- Fear of Negative Appearance Evaluation Scale (FNAES)
	f) satisfaction
	- Self-constructed questionnaire
(5) physical activity:	a) perceived level of daily physical activity
	- the International Physical Activity Questionnaire (IPAQ)
	b) the intervention group: submaximal bicycle test
(5) physical activity:	a) food intake
	-energy (calories)
	- protein
	- fat
	- saturated fat
	- carbohydrates
	- mono- and disaccharides
	- drinks (ml)
(7) other:	- attendance at meetings
	**-** drop-out and reasons for drop-out

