### Sample size calculation

The original sample size calculation in 2009 was based on an anticipated effect of a difference between the groups of 0.45 in terms of Cohen’s d in the primary outcome variable (BMI), with a power (1-beta) of 0.80 and an alpha level of 0.05 (two-sided) in a 2:1 ratio. This ratio was required for analysis of the secondary outcome: the effect of SMS within the intervention group. This resulted in 156 patients to be enrolled in the intervention group and 78 patients in the control group, a total of 234. This number was registered at the Dutch Trial Registry (TC 2450). On behalf of the Grant Foundation (MRace), an interim analysis was performed in May 2014. After inclusion of 150 patients, we applied an interim power analysis to the complete cases. The control group had a reduction from 33.3 ± 6.8 kg/m^2^ to 32.6 ± 6.6 kg/m^2^, an effect of Cohen’s d = 0.10, whereas the lifestyle intervention group showed a reduction from 33.8 ± 4.8 kg/m^2^ to 31.3 ± 5.1 kg/m^2^, an effect of d = 0.52 and a difference of 0.42. For the sample size calculation, we applied the method described by Aberson [71], with a power of 0.90, a two-sided alpha of 0.025 (corrected for the interim analysis) and five repeated measures linearly decreasing. We observed an intercorrelation of about 0.90 between all measurements. Maintaining a ratio of 2:1, the required sample is 84 participants in the lifestyle intervention and 42 in the control group, a total of 126 complete cases. With an observed drop-out proportion of 40%, a total of 210 participants are needed for the study. We anticipated to have a relatively high drop-out rate, because pregnancy leads to exclusion. Note that this sample size calculation is a conservative number, as it is based on a complete case analysis of variance. The intended multilevel analysis provides more power.

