### Statistical analyses

Mixed modelling will be applied for longitudinal analyses of the data by using SPSS version 21. Mixed modelling can efficiently deal with missing data and unbalanced time-points [72]. This analysis will include two levels: the patients will constitute the upper level, and their repeated measures the lower level. First, for each outcome variable a saturated model will be postulated, with the primary or/and secondary outcomes as dependent variables. The saturated models will include treatment group, time, quadratic time, logarithm of time, and all treatment-time interactions as fixed effects. The deviance statistic [73] using restricted maximum likelihood [74] will be applied to determine the covariance structure. Next, the saturated fixed part of the models will be reduced by eliminating insignificant fixed effects using Wald tests, respecting that interaction effects must be nested under their main effects [75]. The significance of the difference between the saturated models and the parsimonious final models will be determined with the deviance statistic using ordinary maximum likelihood. The residuals of the model will be checked for normal distribution, which is necessary for a correctly fitted mixed model. Effect sizes will be calculated by dividing the differences between time-point and baseline estimations and the estimated baseline standard deviation. The definition of Cohen will be used for the interpretation of the effects sizes: an effect size of 0.20 is considered a small effect, 0.50 medium and 0.80 a large effect [76].

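### Measurement stops for women who miss more than 3 of 20 group sessions, so weight goes missing through non-adherence only on the CBT side of the primary comparison

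*Protocol article*

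**What the plan says.** The rule stands under Phase 4 of the intervention description. Treatment ends for a woman who "misses more than 3 out of 20 group sessions. In such cases, the measurements will also stop". The second of these sentences carries the rule over to the data. A second rule follows, that "the intervention and the measurements will also stop when the participant is pregnant". Immediately before both comes a policy that points the other way: "There is an outreach policy to motivate participants to come to the measurement sessions, unless the participant indicates to withdraw from the study".

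The section on the control group gives usual care four follow-up assessments after baseline, with no group sessions and no attendance condition. The primary comparison (Research hypotheses; Outcome measures) is weight at the end of treatment, CBT with or without SMS against usual care. Drop-out is itself an outcome in Table 6 and part of the third hypothesis.

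On missing data, Statistical analyses relies on the statement "Mixed modelling can efficiently deal with missing data and unbalanced time-points". Sample size calculation states "With an observed drop-out proportion of 40%, a total of 210 participants are needed for the study". It does not split that drop-out by arm, links the high rate to pregnancy and does not mention the attendance rule.

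**The concern.** Stopping treatment and stopping measurement are different decisions. Here the second follows automatically from the first, and only in the CBT arms. Women who attend poorly are, on any ordinary expectation, those who lose least weight. Removing their later weights from the CBT side and having no counterpart in usual care selects on a post-randomisation behaviour that is linked to the outcome.

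A stopped woman loses treatment and measurement together. No woman in the CBT arms is therefore observed after this stop, and the data cannot show whether her later weights resemble those of women still in treatment. An analysis plan cannot repair this afterwards, because the weights are never collected.

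Two further things are at stake. The rule turns non-attendance into study drop-out, so part of a secondary outcome is produced by the protocol. It also conflicts with the outreach sentence just before it: women who have not withdrawn are to be encouraged to attend measurements, yet some of them are to be measured no more.

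**Working it through.** **The article's own figures.** Drop-out inflation: 126 / (1 − 0.40) = 210, as stated. Interim effects in complete cases: control 33.3 to 32.6 = −0.7, and 0.7/6.8 = 0.10; intervention 33.8 to 31.3 = −2.5, and 2.5/4.8 = 0.52; difference 0.42, as stated. In BMI points the difference is 2.5 − 0.7 = 1.8.

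**How many women the rule catches.** The article gives no attendance rate. Assume each session is missed independently with the same probability. The share caught is P(4 or more misses of 20). The share of caught women who reach the fourth miss by session 11 (the end of phase 1) is P(4 or more of 11) / P(4 or more of 20).

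| Attendance | Caught by the rule | Of these, caught by session 11 |
|---|---|---|
| 95% | 1.6% | 10% |
| 90% | 13% | 14% |
| 85% | 35% | 20% |
| 80% | 59% | 27% |

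So at 80% to 90% attendance about 73% to 86% of caught women would still have a 3-month weight.

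**If the intervention works.** Let q be the share of CBT women removed, and assume they change as controls did at the interim (−0.7). The all-randomised difference is (1 − q) × 2.5 + q × 0.7 − 0.7 = 1.8 × (1 − q).

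| q | All-randomised difference | Overstatement by 1.8 |
|---|---|---|
| 10% | 1.62 | 0.18 |
| 20% | 1.44 | 0.36 (1.8/1.44 = 1.25) |
| 30% | 1.26 | 0.54 |
| 40% | 1.08 | 0.72 (1.8/1.08 = 1.67) |

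If removed women lose 1.25 points instead of 0.7, the overstatement over the same range of q is 0.12 to 0.50. If they lose nothing, it is 0.25 to 1.00. It is zero only if they do as well as attenders.

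**Does the mixed model repair it?** This was simulated with 30,000 women, 2:1 allocation, five visits and a likelihood-based repeated-measures model with a separate mean for each arm and visit. Stopped women followed the treated course until measurement ended at month 3 and then drifted to the control course.
- 20% stopped: true difference −1.44, complete cases −1.80, mixed model −1.80.
- 40% stopped: true −1.04, complete cases −1.74, mixed model −1.75.

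Nothing is recovered, because the weights before the stop carry no sign of the later return.

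**If the intervention does nothing.** Assume a correlation of r = 0.3 between attendance and 12-month BMI change, SD of change 2.5, and the lowest 30% of attenders removed.
- Complete-case shift = r × SD × φ(z) / (1 − q), with z = −0.524 and φ(z) = 0.348: 0.3 × 2.5 × 0.348 / 0.70 = 0.37.
- Measured women: 140 × 0.7 = 98 CBT and, assuming 20% control loss, 70 × 0.8 = 56. SE = 2.5 × √(1/98 + 1/56) = 0.42.
- Complete-case type I error: about 9% at two-sided 2.5% and 14% at 5%.
- Missing-at-random mixed model, same case, with stop times taken from the attendance model above: the shift falls to about 0.2 (0.17 to 0.26 over attendance of 80% to 90% and two assumed residual SDs, 0.7 and 1.0). With a shift of 0.21 and SE 0.42, type I error is about 4% and 8%; with 0.24 it is about 5% and 9%. Roughly 5% and 8% is a fair summary.

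The mixed-model figures are the relevant ones, because that is the planned analysis. The complete-case figures are shown only for contrast.

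**The case against.** The strongest reply is that the planned analysis is a mixed model and not a complete-case comparison, and that the article reports a correlation of about 0.90 between measurements. Most caught women would have at least a 3-month weight, and the model uses it. This stands in part: in the null case it roughly halves the spurious difference, from 0.37 to about 0.2. It does not bring it to zero, and it gives no protection if women change course once treatment ends.

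A second reply concerns direction. Measurement also stops at pregnancy. The Background says weight loss often leads to ovulation and pregnancy, so that rule may remove good responders, possibly more often from the CBT arms. This stands. A reader might infer that the primary effect is certain to be overstated; the article does not establish the net direction.

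Other stronger readings also go further than the text:
- That caught women have no weight after baseline. Under the attendance model this is the minority.
- That the rule accounts for the 40% drop-out. That figure is all-cause and includes pregnancy. Some poor attenders would also have withdrawn without the rule.
- That the trial compares attenders with a complete control arm. Controls can leave too, through pregnancy or withdrawal.
- That the rule contradicts the schedule in Outcome measures ("All outcome variables are measured at the start of the study, and again at 3 months, 6 months, 9 months and 12 months"). That is a general schedule, to which Phase 4 states exceptions. The real conflict is with the outreach sentence.

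**Conclusion.** The point holds. As written, the protocol makes the primary outcome go missing through non-adherence in the two CBT arms and not in usual care, and no passage restores follow-up. That much rests on the text alone.

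Bias towards the intervention from this rule is likely, on the assumption that poor attenders lose less weight. Its size is assumption-dependent. With 20% removed and a control-like course, 1.8 stands for 1.44 BMI points (25% too large). The 40% case (1.08, 67% too large) is an upper bound in practice, because it attributes all drop-out to this rule. With no true effect, expect a spurious difference of about 0.2 BMI points under the mixed model and a type I error near twice its nominal level. At 95% attendance the rule catches under 2% of women and the effect is small. The interim complete-case effect used to revise the sample size was presumably exposed to the same selection.

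**What to change.** Delete the sentence "In such cases, the measurements will also stop" and leave the treatment-stopping rule untouched, so that the text agrees with the outreach policy. Seek weight at 3, 6, 9 and 12 months in every randomised woman whatever her attendance, unless she withdraws, with pregnancy handled separately. Analyse by randomised arm. Record stopping the intervention and leaving the study as separate events, so that the drop-out outcome is not created by the rule.

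The trial began in September 2009, so an amendment cannot recover weights for women already stopped. For them, use any clinic weight that exists (the article does not say whether any do), report missingness by arm and reason, and add one sensitivity analysis that imputes their later weights from the control course (jump-to-reference).

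The cost is a short amendment and a few more measurement visits, all at times already scheduled. The target of 210 does not change. The estimated effect will probably be smaller.
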